### Patient selection criteria

#### Inclusion criteria

Patients ≥18 and ≤70 years, diagnosed with adenocarcinoma of rectum defined at low-moderate risk of recurrence by T and N extension but also on the basis of CRM involvement measured by MRI: cT2N0 tumors located at ≤2 cm from anal verge, T2N1 or T3N0- N1 tumors, located at >5 cm from anal verge and with infiltration of perirectal fat >5 mm from MRF evaluated by MRI. ECOG Performance Status ≤1. Effective contraception for both male and female patients if the risk of conception exist. Signed written informed consent.

#### Exclusion criteria

Any previous pelvic radiotherapy or treatment for rectal cancer. Presence of metastatic disease or recurrent rectal tumor. History of inflammatory bowel disease or active disease. Any concurrent malignancy. Inadequate bone marrow, liver or renal function (Neutrophils <2000/mm3 or platelets <100.000/ mm3 or haemoglobin <9 gr/dl; Creatinine levels indicating renal clearance of <50 ml/min; GOT and/or GPT >2.5 time the upper-normal limits, UNL; and/or bilirubin >1.5 time UNL). Significant cardiovascular comorbidity. Patients with long QT-syndrome or QTc interval duration >480 msec or concomitant medication with drugs prolonging QTc. Patients who cannot take oral medication.

Patient who have had prior treatment with an HDACi and patients who have received compounds with HDACi-like activity, such as valproic acid. Known or suspected hypersensitivity to any of the study drugs. Concurrent uncontrolled medical conditions that might contraindicate study drugs. Major surgical procedure, within 28 days prior to study treatment start. Pregnant or lactating women.

### Treatment plan

Treatment with VPA will not be matter of dose-finding but a titration strategy will be applied in each patient looking for a serum concentration that is considered useful to produce the desired synergistic effect with radiotherapy and/or chemotherapy. Treatment will be administered orally starting at day -14, until day 21 from beginning of radiotherapy, with a 500 mg slow releasing tablet at evening (Figure 
2). Thereafter, the dose will be increased also using 300 mg tablets (Table 
1). In the morning of day -4, serum level of VPA will be checked and will be adjusted depending on the reached steady level. The target serum level range will be 50–100 μg/ml which represents the recommended values for the treatment of epilepsy. At any time, in case of grade 2 somnolence or fatigue the VPA dose will be reduced by 200 mg/day steps up to reaching grade ≤1 independently of the actual serum level. In case of grade ≥3 somnolence or fatigue VPA will be definitely suspended. In case of asymptomatic QTc prolongation development (QTc >500 ms, or QT prolongation >600 ms,) VPA has to be suspended. Electrolytes and concomitant medications have to be checked and corrected. ECG has to be repeated after 24 hours. If the event is resolved, treatment with VPA can be resumed but the dose will be reduced by -200 mg/day; on the contrary, if QT prolongation is confirmed VPA has to be interrupted
[46, 47] .

**Figure 2 Fig2:**
[figure not shown]
**Schematic timeline of study procedures.** Note. History and physical examination, blood count, biochemistry will be repeated weekly during treatment.

**Table 1 Tab1:** **Valproic acid titration scheme**

Days	Morning dose*	Midday dose*	Evening dose*
-14 & -13	0	0	500
-12 & -11	300	0	500
-10 & -9	500	0	500
-8 & -7	500	300	500
-6 & -5	500	500	500
-4 & -3	500	500	500
-2 & -1	500	500	500

*The interval between doses will be 12 hours on days -14 to -9 and 8 hours from day -8.

In case of symptomatic QTc prolongation development (QTc >500 ms or QT prolongation >600 ms associated with symptoms suggestive of a ventricular tachyarrhythmia), VPA has to be interrupted.

During phase I studies, capecitabine will be administered according to the dose-finding scheme reported above, therefore at a daily dose ranging from 500 mg/m2/bid to 825 mg/m2/bid, for 21 days starting on the day before the beginning of radiotherapy. During the phase II study, capecitabine will be administered at the daily dose indicated as RP2D within phase I studies. This dose might be different without and with VPA, according to results of phase I studies. Toxicity due to capecitabine will be managed by 25% dose-reduction in case of grade 2 adverse events. Treatment with capecitabine will be interrupted upon the occurrence of a grade ≥3 adverse event and restarted once the adverse event has resolved or decreased in intensity to grade 1. The dose will be maintained after the 1st occurrence of the event and will be reduced by 25% at each subsequent occurrence up to a maximum of 50%. Treatment should be discontinued after the 4th occurrence of the event.

RT will be administered according to a short course hypofractionated scheme (SCRT) consisting of five fractions each of 5 Gy for 5 consecutive days for a total dose of 25 Gy.

Both in phase I and II studies, surgical operation, will be performed 8 weeks after the last day of radiotherapy. To explore diagnostic accuracy of pre-surgical rectal biopsy, all surgical operations will include a preliminary rectal biopsy, that will be performed after the induction of anaesthesia. The biopsy specimen will be examined intraoperatively; however, the result of intraoperative pathology will not influence subsequent surgical behaviour. An anterior resection or an abdominal perineal resection, with total mesorectal excision, will be performed on the basis of restaging. Fecal diversion to protect the anastomosis will be performed by the means of a loop ileostomy; and ileostomy reversal will be performed after endoscopic assessment of anastomotic integrity. All resection specimens will be examined by two independent dedicated rectal cancer pathologists and pathologic staging, ypTNM and TRG, will be determined according to AJCC guidelines
[48]. The number of examined/involved lymph nodes, tumor differentiation, lymphatic and venous invasion, and status of proximal, distal, and circumferential resection margins will be also reported.

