**Figure 1 Fig1:**
[figure not shown]
**V-shoRT-R3 study design. a)** Scheme of phase I study, **b)** Plan of Phase II study.

Four increasing dose levels of capecitabine (L1-L4) are planned: 500, 650, 750, and 825 mg/m^2^/bid. Three further intermediate dose levels (L1b, L2b, L3b), are also provided in case MTD is reached (Figure 
1a).

At each dose level, a cohort of 3 patients (pts) will be enrolled. Within each trial, MTD will be defined as the dose producing DLT in 2 pts (any grade 3 non-hematologic or grade 4 hematologic toxicity occurring within 5 weeks from day 1 of treatment).

Patients will be enrolled consecutively according to the available slot. However, the V + trial will begin after the enrollment of the first 2 cohorts in the V- trial. Subsequent cohorts in the V + trial will be enrolled only with dose levels of capecitabine that have not been defined as MTD in the V- trial.

The dose level immediately lower than the MTD will be the recommended phase II dose (RP2D); within each study, the cohort treated at the RP2D will be expanded up to 9 pts.

According to the study design, and if MTD is reached or not, sample size of each phase I study will vary from 2 to 33 pts.

Patients eligible at a time when phase I studies are still ongoing but a treatment slot is not available will be offered to enter the first time-window of the phase II trial (see below).

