### Adverse events

Adverse events will be graded according to the Common Terminology Criteria for Adverse events of the National Cancer Institute (CTCAE-NCI) version 4.0.

Adverse events will be assessed at the following times: at baseline (within 3 weeks before the initiation of any treatment), at days 8, 15, 22, 29, before surgery, 1 and 2 months after surgery. In addition, only in patients receiving VPA, adverse events will be assessed at day -4.

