### Statistical analysis of phase II

Phase II analysis will be performed according to the intention-to-treat strategy. Analyses will be performed separately for the two planned comparisons. In each comparison, TRG1 rate is defined as the rate of patients out of those randomized who will experience a complete pathological regression according to Mandard modified scoring system (responders). Patients who will not achieve a TRG1 will be defined as non-responders. Patients who will not undergo primary surgery because of progressive disease will be defined as non-responders. TRG1 rates will be compared with chi-square test in a 2×2 contingency table (responders/non-responders x treatment arms).

For each patient and for each type of toxicity, the worst degree suffered during treatment will be used for the analysis. Two sets of statistical analyses will be performed to compare toxicity. In the first set the whole pattern of toxicity (all grades) will be considered for each item; analysis will be done by a linear rank test. In the second set toxicity will be defined as severe (mostly including grade 3 or higher) and not severe (mostly including grades up to 2) and analysis will be performed by Fisher’s exact test.

Due to the small sample size, statistical analysis of biomarkers data will be conducted with the aim of hypothesis generation. Biomarkers that might change over time as a consequence of treatment, levels before and after treatment will be compared with appropriate statistical tests, based on the type of data.

QoL will be described according to EORTC rules
[58, 59].

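### The capecitabine rule cuts the dose by 25% for a grade 2 event but keeps it unchanged on restart after a first grade 3 or 4 event

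*Protocol article*

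**What the plan says.** The capecitabine rules stand in the protocol article under Treatment plan, in the text after the valproic acid (VPA) titration table.

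- **Grade 2:** "Toxicity due to capecitabine will be managed by 25% dose-reduction in case of grade 2 adverse events". No occurrence count is attached.
- **Grade 3 or higher:** "Treatment with capecitabine will be interrupted upon the occurrence of a grade ≥3 adverse event", with restart once the event has resolved or fallen to grade 1.
- **Restart dose:** "The dose will be maintained after the 1st occurrence of the event and will be reduced by 25% at each subsequent occurrence". Reductions are capped at 50%, and treatment stops after the fourth occurrence.

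Three other places bear on this.

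- **VPA, same section:** grade 2 somnolence or fatigue leads to steps of 200 mg/day downwards, and "In case of grade ≥3 somnolence or fatigue VPA will be definitely suspended".
- **Study design, Phase I:** a dose-limiting toxicity (DLT) is "any grade 3 non-hematologic or grade 4 hematologic toxicity occurring within 5 weeks from day 1 of treatment".
- **Adverse events:** after baseline, assessments fall "at days 8, 15, 22, 29, before surgery, 1 and 2 months after surgery".

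On the start day, Treatment plan gives phase I capecitabine "for 21 days starting on the day before the beginning of radiotherapy". The Abstract and the Phase I design give it on days 1 to 21, with radiotherapy on days 1 to 5.

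**The concern.** A toxicity rule should respond at least as firmly to a worse event as to a milder one. Here the first grade 2 event costs a quarter of the dose, while the first grade 3 or 4 event costs a pause and no reduction. The text gives no reason for this order, and the article's own VPA rule for somnolence and fatigue runs the other way.

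What is at stake is patient safety. Patients with the more severe toxicity are re-exposed at a higher daily dose than patients with the milder one. In the arms that combine both drugs, VPA is scheduled to day 21, so it may still be running at that point. The recommended phase II dose is a starting dose given under a reduction rule, so that rule is part of the treatment that phase II tests in its two capecitabine arms.

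**Working it through.** **1. What the grade 3 or higher rule means.** In the restart sentence, the event refers back to the grade 3 or higher event in the sentence before. The printed steps are then 100% after the first occurrence, 75% after the second, 50% after the third, and stop after the fourth. This fits the stated 50% cap and the stated stop.

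**2. The other reading.** Suppose the event was also meant to cover grade 2. Then a first grade 2 event both triggers an immediate 25% cut and leaves the dose unchanged. The paragraph contradicts itself, so this reading does not repair it.

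**3. Daily dose after the first event.** The inputs are the four main dose levels in the Phase I design. After grade 2 the dose is 0.75 × level. After a first grade 3 or higher event it is 1.00 × level, if there was no previous cut.

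| Level | After grade 2 (mg/m2 bid) | After first grade ≥3 (mg/m2 bid) |
|---|---|---|
| L1 | 0.75 × 500 = 375 | 500 |
| L2 | 0.75 × 650 = 487.5 | 650 |
| L3 | 0.75 × 750 = 562.5 | 750 |
| L4 | 0.75 × 825 = 618.75 | 825 |

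The ratio is 1/0.75 = 1.33 at every level. A patient already cut to 75% for grade 2 restarts at 75% after a first grade 3 or higher event. For that patient there is no inversion, but also no further reduction.

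**4. Total dose, event found on day 8.** Assume a 21-day course with 7 full days already taken, 14 days left, and missed days not made up.

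- Grade 2: (7 + 14 × 0.75)/21 = 17.5/21 = 83.3% of plan.
- Grade 3 or higher, off drug for k days: (21 − k)/21.
  - k = 3: 18/21 = 85.7%
  - k = 4: 17/21 = 81.0%
  - k = 7: 14/21 = 66.7%
- Break-even: k = 14 × 0.25 = 3.5 days.

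For an event found on day 15, with 7 days left, the break-even falls to 7 × 0.25 = 1.75 days.

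**5. Can the later reductions act?** If events and recovery are seen only at scheduled visits, an event found on day 8 can restart on day 15 at the unchanged dose and run to day 21. The next visit, day 22, is after the course. An event found on day 15 has no restart. On that timetable the first restart dose is the only one that operates. Unscheduled contacts could change this.

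**6. Start day.** Days 1 to 21 end on day 21. A 21-day course begun the day before day 1 covers that day plus 20 more, so it ends on day 20. The difference is one day.

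**The case against.** The strongest reply is that the restart dose is only part of the response. A grade 3 or higher event stops capecitabine completely until recovery, while a grade 2 patient never stops. With restart on day 15 after an event on day 8, the worse event leads to 66.7% of the planned total against 83.3% for the milder one. This stands: the inversion is in the daily restart dose and does not generally carry over to total exposure. It does not explain why the dose on re-exposure should be higher after the worse event.

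A reader might infer that a phase I patient with a DLT must go back to the level that caused it. The documents do not say so. Every DLT is grade 3 or higher, and the rule names no phase and no DLT exception, so the restart is not excluded. But the rule follows directly on the phase II dosing sentences, and a full protocol may take DLT patients off drug. The DLT window of 5 weeks also runs past the end of capecitabine, so a late DLT has no restart.

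A reader might also expect centres to dose differently because of this text. Nothing shows that centres work from the article, so that is conjecture.

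The VPA comparison is supporting evidence only: it concerns another drug and two symptoms. Even so, the article resumes VPA at a lower dose after a resolved asymptomatic QTc prolongation, which again is the expected direction.

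**Conclusion.** The concern holds for the restart dose. As printed, a first grade 3 or 4 event leads back to a daily dose 1.33 times the dose that follows a first grade 2 event, in patients with no previous cut. If the sentence was meant to cover grade 2, it contradicts the grade 2 cut instead. On a phase-II-only reading the inversion remains in the two capecitabine arms.

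It would go too far to conclude that the maximum tolerated dose or the recommended dose is biased upwards: both describe a starting dose, and nothing in the article gives phase II a different reduction rule. Alpha, power and sample size are untouched. The effect on the phase II toxicity comparison should also be small. For each toxicity type "the worst degree suffered during treatment will be used for the analysis", so a patient who has had a grade 3 event will mostly already count as severe for that item.

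The total-dose figures rest on the assumptions of an event found on day 8 and missed days not made up. The point should be corrected because the rule is explicit, bears on patient safety and is cheap to repair. The start-day mismatch is a separate, minor point.

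**What to change.** State one rule ordered by grade: the restart dose after any grade 3 or higher event is never above the dose that follows a grade 2 event. One example is restart at 75% at the first occurrence; the later steps are a clinical choice. At L2 to L4 a 75% restart also lies below the next lower main level (487.5 < 500, 562.5 < 650, 618.75 < 750).

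If keeping the dose after a first occurrence was meant for grade 2, remove the immediate grade 2 cut and state the reduction for grade 3 or higher.

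In either case, say which phases the rule covers and what happens to a phase I patient after a DLT. Separately, give one capecitabine start day and keep day 1 as the first radiotherapy day.

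This is a change to a dosing rule as well as to its wording. With the 75% restart, its cost is somewhat less capecitabine for some patients after a first grade 3 or higher event. The DLT definition, the escalation rule and the sample size stay as they are.

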### Assessment and procedures

Assessment and procedures, including those for exploratory objectives (see below), are illustrated in Figure 
2.

### Adverse events

Adverse events will be graded according to the Common Terminology Criteria for Adverse events of the National Cancer Institute (CTCAE-NCI) version 4.0.

Adverse events will be assessed at the following times: at baseline (within 3 weeks before the initiation of any treatment), at days 8, 15, 22, 29, before surgery, 1 and 2 months after surgery. In addition, only in patients receiving VPA, adverse events will be assessed at day -4.

### FDG-Positron Emission Tomography (PET) imaging

MRI and other conventional imaging modalities such as EUS and CT are unable to differentiate post-radiation inflammation and fibrotic changes from viable tumor in the residual lesion following preoperative treatment
[49, 50]. In contrast, metabolic imaging with [18 F] 2-fluoro-2-deoxy-D-glucose positron emission tomography (FDG-PET) may be more valuable in this respect as the high glycolitic activity of tumor cells can be utilized to discriminate fibrosis from viable tumor tissue
[51]. In the neoadjuvant setting, a strong correlation between FDG standardized uptake value (SUV) changes and pathologic response has been demonstrated in different tumors
[52–54], including rectal cancer
[55]. Our group has previously reported that early metabolic change evaluated by FDG-PET is able to predict pathologic tumor response
[56] and outcome
[57] in rectal cancer. Thus, FDG-PET/CT scans are planned at baseline and on day 11 (+/- 2) in patients enrolled in phase II study, to validate the ability of early metabolic change to predict TRG and outcome. For each tumor volume, maximal standardized uptake value (SUV-max, the maximum pixel value in the lesion), SUV-mean (the average SUV value in the lesion) and Total Lesion Glycolisis (TLG, SUV-mean x metabolic tumor volume) will be calculated. A responder patient, consistent with our previous studies, will be define according to reduction of SUV or TLG parameters of 50% or more compared to baseline. Therefore, patients with any change below this threshold will be defined as non-responder. Further thresholds will be eventually explored only in case of failure (lack of predictive ability) of the proposed validation.

### Pharmacodynamic, pharmacogenetic and pharmacokinetic studies on tumor and blood samples

Tumor and normal mucosa samples will be collected only in patients enrolled in the four-arm phase II study: at baseline (possibly within the diagnostic rectal biopsy) and at surgery for all patients and at day -4 in patients assigned VPA.

Baseline tumor expression of TP, TS, VEGF, RAD51 and XRCC1, will be compared with normal mucosa and with tumor expression at the following time points as pharmacodynamic/predictive markers of treatments (analyzed by real-time PCR and immunohystochemistry). In fact, as reported above, several evidences, by our group and others, including preliminary results, suggested a crucial role of the modulation of the expression of TS and TP in the synergism observed between HDACi and fluoropyrimidine. On the other hand, TP showed a strong sequence homology to the pro-angiogenic platelet derived endothelial cell growth factor (PD-ECGF), and may contribute to angiogenesis, tumor progression and metastasis. However, several reports have clearly shown that HDACi inhibit tumor-induced angiogenesis by regulating VEGF production and signaling. Moreover, the expression DNA repair genes, such as RAD51 or XRCC1, affecting sensitivity to RT and or chemotherapeutics, can be also regulated by HDACi.

Histones and proteins acetylation (H&P-Ac) measured at all the time points and HDAC isoforms evaluated at baseline represent additional pharmacodynamic/predictive specific markers of VPA HDACi activity.

Peripheral blood samples will be collected at baseline, on day -4, 1, 8, 11, 22 and at surgery. VPA serum level will be measured by a valproate test at all time points and correlated with H&P-Ac, measured on peripheral PBMC as additional surrogate pharmacodynamic markers of VPA activity by multiparametric flowcytometry.

Polymorphisms of genes that may affect activity and toxicity of radio-chemotherapy such as DPD, TS, XRCC1, GSTP1, RAD51 and XRCC3, will be analyzed on baseline samples by pyrosequencing technology.

Circulating Endothelial Cells (CEC) and Progenitors (CEP) counts will be analyzed as surrogate marker of tumor angiogenesis at baseline, on day 1, 11 and at surgery by multiparametric flowcytometry.

### Quality of life assessment

Quality of Life (QoL) will be assessed in patients enrolled in the randomized four arm phase II study by the EORTC QLQ-C30, version 3.0, and the EORTC QLQ-CR29 questionnaires that will be filled in by patients before treatment, at the end of radiotherapy (D8) and of chemotherapy (D22), before surgery and 30 days after surgery
[58, 59].

### Adjuvant treatment

There is no general agreement on the benefit of adjuvant CT after preoperative CRT. The only study, EORTC trial 22921, to formally evaluate the benefit of adjuvant CT after preoperative CRT failed to demonstrate a significant impact on survival of postoperative chemotherapy
[33]. Moreover, emerging data suggest a significant correlation between pathologic response to preoperative chemo-radiotherapy and oncologic outcomes, evidencing the favorable prognostic value of pathologic complete response
[60–62]. These data generate the hypothesis that it might be reasonable to link the decision on adjuvant treatment to the pathologic response obtained after neoadjuvant treatment. However, given the absence of definitive evidence on this topic, and considering that the impact of adjuvant treatment in this protocol will only affect secondary end-points, decision regarding adjuvant chemotherapy will be decided by the investigators according to the policy commonly adopted by their Institution in clinical practice.

### Follow up

Patients will have follow-up evaluation every three months for three years and every six months during the following two years. Patients who have discontinued study treatment for reasons other than progressive disease will enter follow-up.

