### Objectives

The primary objective of the Phase I study is to determine the MTD of capecitabine given alone or in combination with valproic acid during preoperative SCRT.

The primary objective of the phase II comparative study is to explore whether the addition of valproic acid and/or capecitabine to SCRT before optimal radical surgery might increase the rate pathologic complete tumor regression (reported as tumor regression grade 1; TRG1) in patients with low-moderate risk rectal cancer.

Within each planned phase II comparison, secondary objectives include the evaluation of local control, disease free survival and overall survival, pathological CRM negative (>1 mm) and lymph node negative rate, short and long-term toxicity, surgical complications, and quality of life. The study also aims to validate the predictive role of early tumor metabolic changes measured by positron emission tomography (PET) scan (both phase I and II) and to assess the diagnostic accuracy of pre-surgical rectal biopsy, performed after the induction of anaesthesia in all surgical operations and analysed by intraoperative pathology (both phase I and II).

A translational sub-study is also planned, within the phase II trial, with several aims: (a) to compare the expression of several biomarkers (TP, TS, VEGF, RAD51, XRCC1, Histones and proteins acetylation, HDAC isoforms) in the tumor and normal mucosa, at baseline and at different time points during and after treatment; (b) to analyse polymorphisms of genes that may affect activity and toxicity of chemo-radiotherapy (DPD, TS, XRCC1, GSTP1, RAD51 and XRCC3) on DNA from peripheral blood; (c) to evaluate Circulating Endothelial Cells (CEC) and Progenitors (CEP) counts on peripheral blood at baseline and at different time points during and after treatment; (d) to evaluate Histones and proteins acetylation (H&P-Ac) of PBMCs at baseline and at different time points during and after treatment.

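### The follow-up rule, as worded, leaves out patients who stop treatment for progression, which conflicts with overall survival as an intention-to-treat secondary endpoint

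*Protocol article*

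**What the plan says.** The Follow up section of the protocol article has two sentences. The first sets the schedule without restriction: "Patients will have follow-up evaluation every three months for three years and every six months during the following two years". The second governs entry after early stopping: "Patients who have discontinued study treatment for reasons other than progressive disease will enter follow-up".

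Three other statements bear on this:

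- Objectives, for each phase II comparison: "secondary objectives include the evaluation of local control, disease free survival and overall survival".
- Statistical analysis of phase II: "Phase II analysis will be performed according to the intention-to-treat strategy".
- The same section, for the primary endpoint: "TRG1 rate is defined as the rate of patients out of those randomized", and "Patients who will not undergo primary surgery because of progressive disease will be defined as non-responders".

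The article does not say how patients who progress early are handled for overall survival. It also does not say whether surgery is part of study treatment.

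**The concern.** If every patient were followed whatever the reason for stopping, the qualifier about progression in the second Follow up sentence would serve no purpose. Its natural reading is that patients who stop for progression are not followed.

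Stopping for progression happens after randomisation and is related to outcome, and these patients can be expected to have a higher risk of death than the rest. A survival curve that loses sight of them treats their later risk as equal to that of patients who stayed progression-free. Overall survival is then too high. If the proportion stopping for progression differs between the two sides of a comparison, the error does not cancel.

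The plan guards its primary endpoint against this loss by counting progressors as non-responders among all randomised patients. It gives overall survival no matching protection.

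**Working it through.** **1. The plan's own figure.** The only sample size stated for phase II is 86, for the rate of complete regression (TRG1): 5% against 20%, one-sided alpha 0.10, power 80%. With pooled variance under the null and no continuity correction, the number per side is

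n = [z(0.90)·√(2·0.125·0.875) + z(0.80)·√(0.05·0.95 + 0.20·0.80)]² / 0.15²

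= [1.2816·0.4677 + 0.8416·0.4555]² / 0.0225 = 42.9, so 43 per side and 86 in total.

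Power at 43 per side is 0.8005. The stated figure reproduces. It rests on TRG1 at surgery among all randomised patients, so the follow-up rule does not touch it. No event count or power is stated for overall survival.

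**2. Who falls under the clause.** The clause concerns stopping study treatment. Radiotherapy takes five days and capecitabine 21 days. For valproic acid: "Treatment will be administered orally starting at day -14, until day 21 from beginning of radiotherapy". Surgery "will be performed 8 weeks after the last day of radiotherapy", that is, at about day 5 + 56 = day 61.

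- Narrow reading (drugs and radiotherapy only): the clause can apply only up to about day 21, and for five days in the radiotherapy-alone arm.
- Wide reading (surgery included): it can apply throughout the preoperative period, about two months, and takes in the patients not operated on because of progression whom the analysis section mentions.

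The article does not settle which reading is meant.

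**3. Size of the effect on overall survival.** The documents give neither a rate of stopping for progression nor a survival rate, so the following are assumptions:

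- d = proportion stopping for progression, 1% to 5%;
- S = 5-year survival in the others, 80%;
- s = 5-year survival in progressors, 10% to 30%.

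True survival in all randomised patients is (1 − d)·S + d·s. If progressors are omitted, or censored before their deaths, the estimate is about S. The overstatement is therefore d·(S − s).

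| d | Patients out of 86 | Overstatement, s = 30% | Overstatement, s = 10% |
|---|---|---|---|
| 1% | 0.9 | 0.01 × 50 = 0.5 points | 0.01 × 70 = 0.7 points |
| 2% | 1.7 | 0.02 × 50 = 1.0 | 0.02 × 70 = 1.4 |
| 5% | 4.3 | 0.05 × 50 = 2.5 | 0.05 × 70 = 3.5 |

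**4. Size of the effect on a comparison.** With d₁ and d₂ on the two sides and the same S and s, the error in the survival difference is (d₁ − d₂)·(S − s). It is zero when the two rates are equal. At 1% against 5% (0.4 against 2.1 patients out of 43) it is 0.04 × 50 to 0.04 × 70 = 2.0 to 2.8 points, to the apparent advantage of the side with more early progression. This illustrates the mechanism only; no document says that the rates will differ.

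**The case against.** The strongest reply is that the exclusion is implied, not stated. The schedule sentence covers patients without restriction, and the next sentence may have been meant inclusively, to say that stopping early does not end follow-up. A journal article condenses the full protocol, which may provide for vital status after progression. This tempers the point but does not remove it. The published sentence singles out progression, and a site that follows it literally would not collect these data.

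A second reply is that the clause reaches few patients. Treatment is short, eligibility excludes metastatic disease, and a patient found to have progressed after day 21 has completed drug treatment rather than discontinued it. This stands on the narrow reading of study treatment. It is weaker on the wide reading, which is open because surgery is described within the Treatment plan.

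A reader might also infer more than the documents support:

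- *That intention-to-treat analysis of survival becomes impossible.* It does not. The patients stay in their randomised arm and can be censored at last contact. The estimate is biased, not unobtainable.
- *That all early progressors are censored at about two months.* This assumes that surgery counts as study treatment, which the article does not say.
- *That censoring must differ by arm because the treatments are meant to change early progression.* The stated phase II aim is a higher TRG1 rate. Differential progression is possible but is not claimed.
- *That up to about a third of deaths would be lost.* Assuming 2-4 progressors who nearly all die, and 13-22 deaths in total, gives 2/22 = 9% to 4/13 = 31%. These ends pair opposite extremes of assumptions, none of which comes from the documents.

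**Conclusion.** The point holds in a limited form. The Follow up wording conflicts with overall survival as a secondary objective and with the intention-to-treat statement, and the passages need to be reconciled. Followed literally, the rule produces informative censoring that overstates overall survival, by roughly 0.5-3.5 percentage points at five years under the assumptions shown. It could bias a comparison if early progression differs between arms.

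TRG1 and the sample size of 86 are unaffected. For disease-free survival the progression would probably already be the event. Severity is minor to moderate: the trial is exploratory, the endpoint is secondary, and the number affected is probably small. It still merits correction while follow-up is running, because survival status not collected at the time may be hard to recover later.

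**What to change.** Replace the second sentence of the Follow up section with: *All randomised patients, including those who discontinue because of progressive disease or are not operated on, will be followed for survival status for five years; after progression a vital-status check is sufficient.*

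If the full protocol already provides for this, align the published wording with it. The cost is one sentence and vital-status contacts for a handful of patients (about 1 to 4 of the 86 under the assumptions above). The change concerns data collection only; treatment, the primary analysis and the sample size stay as they are.
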